### Trial summary

The trial is a pragmatic, multicentre, two-arm, double-blind, cluster randomised controlled trial of a computer software intervention designed to reduce the effects of a vigilance decrement in breast cancer screening. The intervention changes the order in which the readers examine the batches of mammograms. The centres will be NHSBSP centres with digital mammography equipment. A cluster for randomisation comprises a batch of mammograms (approximately 30 to 50 women’s mammograms). Intervention batches will be examined in the opposite order by the two readers (one in appointment order and one in reverse appointment order). Control batches will be read in the same order as one another as is current standard practice. The unit for analysis is the individual woman’s outcome.

Standard practice is for both readers to read the batch of mammograms in the order in which the women were booked in for their appointments. In the control group, both readers will read each batch in the same order as one another, but this may be in appointment order or in reverse appointment order (↓↓ or ↑↑). In the intervention group, both readers will read the mammograms in the order opposite one another (↓↑ or ↑↓). This design blinds the readers because if they read in the reverse order, they will not know if they are reading the intervention or control group. The study software which will be used to run the trial will be embedded in the National Breast Screening Service (NBSS) software system in every English breast screening centre as part of routine updating of the NBSS system.

The pilot study will be conducted in three screening centres for 2 weeks to ascertain practical issues with implementation and to test the data collection tool, which will extract the results from the screening centres’ electronic database (NBSS). Concurrently, a survey of all English breast screening centres will be conducted to ascertain key characteristics relevant to the trial which may differ between centres, such as the method of arbitration used. These details will be described in the report and considered in the statistical analysis of the trial to ascertain whether the effectiveness of the intervention is affected by these characteristics.

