#### Secondary analyses

To determine whether the disagreement rate between readers, interval cancer rate and recall rate are different between the intervention and control groups (secondary aims 1, 2 and 3), the same methods as described for the primary analysis above will be used. The PPV of cancer detection in each study arm will be calculated as the proportion of women recalled who are found to have cancer (secondary aim 3).

The effects of the trial introducing the reverse reading order (secondary aim 5) will also be analysed. The recall and cancer detection rates for the two reading groups which make up the control arm will be compared (↓↓ compared to ↑↑). Models will be constructed in the same way as the primary analysis, but using reading order, not trial group membership, as the predictor of cancer detection rate and recall rate.

To generate secondary outcome 4 (estimates of cost-effectiveness), the primary outcome from the trial will be used as an input into a health economic model of breast cancer screening. This model will be developed by expanding an earlier breast cancer model described by Campbell *et al*. [12] and will predict lifetime costs and effects for both the intervention and control arms. The model simulates the underlying breast cancer disease process according to prognosis upon presentation and includes adjuvant therapies, the long-term risk of recurrence (both local and metastatic) and treatment and long-term survival following recurrence. It will be used to model the changes in costs, life-years and quality-adjusted life years brought about by a potential change in the cancer detection rate.

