### Power and sample size

Currently, 14,700 cancers are detected by screening each year, and the cancer detection rate is 7.8 per 1,000 women screened [3]. Detection of one extra cancer case per 2,000 women screened would increase the cancer detection rate to around 8.3 cancers per 1,000 women screened. To detect this change of 0.5 cancers per 1,000 women using a two-tailed test at 80% power and 5% significance, 501,361 women are required in each arm.

As randomisation occurs at the batch level, however, collected data are clustered and this must also be taken into consideration. The sample size of a clustered study must be increased by the design effect (DE), which is calculated as *DE* = 1 + (*m* - 1)*ρ* for a given intraclass correlation coefficient (ICC; *ρ*) and cluster size (*m*). The ICC was calculated using previous data in a logistic binomial Gaussian model (method B) with 1,000 Monte Carlo simulations [13]. Hence, using the ICC of 0.002 and a cluster (batch) size of 40 women produces a DE of 1.09, increasing the sample size required to 546,890 in each arm.

There is no adjustment for crossover, because once the intervention is applied to a screening centre, each batch will automatically be randomly assigned to the intervention or control group by the NBSS computer system and the intervention will be applied automatically by the same system. A woman could be lost to follow-up if her NBSS records have not been updated or if she is recalled from screening for further tests and does not attend her follow-up appointment. This is uncommon, however, so we have assumed low dropout rates of 3,500 women in each arm, inflating the sample required to 550,390 in each arm. Therefore, as detailed in Figure 1, the overall sample size required is for 1,100,780 women, or 44 breast screening centres for 1 year (On the basis that in England there are 82 centres each screening around 25,000 women per year).

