## Discussion

The experimental design is between subjects, so readers will not be burdened with reading cases twice (once in each experimental condition). This design has lower statistical power than a within-participant approach, however, so recruitment targets are high to achieve 80% power. Sensitivity analysis for the estimate of effect size indicates that it is very sensitive to small changes in effect size. If the effect size is as low as 200 extra cancers detected per year in England, it may still be considered clinically significant, but overall sample size would need to be 14 million women to detect such an effect. Achieving a sample of this size would be unrealistic; therefore, there is a risk of the trial being underpowered. However, an effect size of 200 extra cancers detected in England each year would be detectable in the form of a surrogate for cancer detection rate, which is the rate of disagreements between readers. This parameter is included as a secondary outcome. If recruitment targets are not met, then the rate of disagreements, as a surrogate for cancer detection rate, may have to be used as the primary outcome.

One possible mechanism for harm from the intervention is associated with reading the cases in reverse appointment order, which is not currently standard practice. To blind the readers to group allocation, however, reading in reverse appointment order is present equally in the intervention and control groups, so a two-tailed test would not detect this harm. Therefore, a secondary analysis of recall rate and cancer detection rate of cases read in appointment order and reverse appointment order will be carried out to determine whether reading a batch in reverse appointment order affects performance.

This study is a pragmatic multicentre, two-arm, double-blind, cluster randomised controlled trial of a computer software intervention designed to reduce the effects of a vigilance decrement in breast cancer screening. The intervention and randomisation are applied automatically using computer software, thus reducing the cost of running the trial and limiting the possibility of allocation and treatment bias. This study design also reduces the administrative burden on participating centres, thus removing one of the barriers to participation. The trial is double-blinded because neither the women screened nor the readers will be aware of whether each batch is in the intervention or control group.

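### The opposite-versus-same-order contrast equals the gain over current practice only if reverse reading has no effect, and the plan names no estimate against current practice although it uses this contrast in the economic model

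*Protocol article*

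**What the plan says.** The Trial summary of the protocol article defines current practice: "Standard practice is for both readers to read the batch of mammograms in the order in which the women were booked in". It also says of the control arm: "Control batches will be read in the same order as one another as is current standard practice". The paragraph after that explains that control batches may be read by both readers in appointment order or by both in reverse. Recruitment and randomisation gives the four reading-order groups equal probability, so half of the control arm is both-reverse.

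The reason given is blinding: a reader who sees a reversed batch cannot tell which arm it belongs to. The Discussion acknowledges that reverse reading is not standard and might do harm, and adds that "reading in reverse appointment order is present equally in the intervention and control groups, so a two-tailed test would not detect this harm".

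The safeguard, under Secondary analyses, is that "The recall and cancer detection rates for the two reading groups which make up the control arm will be compared". Trial aims and outcomes describes the same comparison. The article states no power for it. The cost-effectiveness aim compares the intervention with the control arm and takes the primary outcome as the model input.

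**The concern.** A service that adopted opposite-order reading would move from no reversed reads per batch to one. Any effect of a reversed read is part of what it would get. The primary contrast removes that effect by design, because each arm has the same share of reversed reads.

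If reverse reading lowers detection, the primary estimate exceeds the gain that a screening service would see, and the economic model inherits the difference. If reverse reading raises detection, the primary estimate understates the gain. The documents give no basis for choosing between the two directions. The question is how much the planned check on reverse reading can say, and whether the plan states an estimate against current practice anywhere.

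**Working it through.** **Inputs** (Power and sample size, unless stated)
- Rates: "the cancer detection rate is 7.8 per 1,000 women screened"; the target "would increase the cancer detection rate to around 8.3 cancers per 1,000 women screened". The difference is 0.5 per 1,000.
- Stated size: "using a two-tailed test at 80% power and 5% significance, 501,361 women are required in each arm".
- Clustering: "using the ICC of 0.002 and a cluster (batch) size of 40 women produces a DE of 1.09".
- After clustering 546,890 per arm; after dropout 550,390 per arm.
- Recall rate 40 per 1,000 (Background).
- Four equal groups (Recruitment and randomisation).

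**Step 1: reproduce the plan's figure.**
n per arm = (1.960 + 0.842)² × [0.0078 × 0.9922 + 0.0083 × 0.9917] / 0.0005² = about 501,395, against the stated 501,361. It reproduces. The ratio 546,890 / 501,361 gives a design effect of 1.0908. The rounded ICC gives 1 + 39 × 0.002 = 1.078. The gap is consistent with an unrounded ICC of about 0.0023, and both values are carried below.

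**Step 2: what the primary contrast estimates.**
Write FF, RR and Int for the detection rates in both-forward control, both-reverse control and the two intervention groups combined, and D = RR − FF. With equal-sized control halves:

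Int − FF = [Int − (FF + RR)/2] + (RR − FF)/2 = primary contrast + D/2.

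On the scale of rate differences this is exact and needs no model of how reversal acts. If the primary contrast is +0.5 per 1,000:

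| D (per 1,000) | Gain over both-forward (per 1,000) |
|---|---|
| −1.0 | 0.00 |
| −0.5 | 0.25 |
| 0 | 0.50 |
| +0.5 | 0.75 |

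**Step 3: what the planned check says about D, for cancer detection.**
- Women per control half: 546,890 / 2 = 273,445; effective number 273,445 / 1.0908 = about 250,680.
- SE(D) = √(2 × 0.0078 × 0.9922 / 250,680) = 0.248 per 1,000.
- 95% CI half-width = 1.96 × 0.248 = 0.49 per 1,000, so about 0.24 for D/2.
- Power for a difference of 0.5: 51% (7.8 to 8.3) or 53% (7.8 to 7.3). The range is 51-54% over design effects of 1.078 to 1.091 and 546,890 to 550,390 per arm.
- Power for a loss of 0.75: 87%; for a loss of 1.0: 99%.
- 80% power needs a loss of about 0.68 or a gain of about 0.71.

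**Step 4: the same check for recall**, assuming the same design effect. From 40 per 1,000, power is 80% for a change of about 1.6 per 1,000 and 95% for 2 per 1,000.

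**Step 5: a direct contrast with current practice.**
SE(Int − FF) = √(0.0078 × 0.9922 × 1.0908 × (1/550,390 + 1/275,195)) = about 0.21 per 1,000. Power for 0.5 is about 64% with the variance taken at 7.8 per 1,000, and about 63% with separate variances. The primary contrast has SE √(0.0078 × 0.9922 × 1.0908 × 2/550,390) = about 0.18.

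**The case against.** The strongest defence is that the plan does what it says. The stated aim is opposite versus same order, and the primary contrast estimates that. The mixed control is deliberate, protects reader blinding and is disclosed, as is the possible harm. The standard-practice wording can be read as describing only that both readers use the same order, and the next paragraph spells out both control versions. All of this stands. A reader might infer that the primary comparison is biased or invalid; the documents do not support that.

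A reader might also infer that the check has roughly even odds of missing a loss as large as the target gain. That confuses D with D/2. Only one reader is reversed in an intervention batch, so D of −0.5 costs 0.25 on adoption. Cancelling the whole 0.5 needs D of −1.0, which the check would find with about 99% power. Recall is better covered still. Nor does the article say that a null result will be taken as proof of no harm.

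It might also seem that the check wastes half the data. For the double-read outcome this is largely inherent. Every intervention batch has exactly one reversed reader, so under a symmetric additive effect those groups add nothing about D. Only an analysis of each reader's own decisions could use them.

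Finally, intervention versus both-forward is the sum of the primary estimate and half of D, both already planned, and the SAP, which is not shown, may set it out. That limits the point but does not remove it. The article itself fixes the description of control, the check on reverse reading and the economic input. It does not say that the two estimates will be combined.

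**Conclusion.** The point holds as a limit on interpretation, and should be addressed. The primary contrast is valid for its aim, but it equals the gain over current practice only if D is zero. The article names no estimate of that gain, and uses the primary contrast in an economic evaluation meant for the NHS.

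Even if D were observed as exactly zero, D/2 would remain uncertain by about 0.24 per 1,000 either way, close to half of the target gain. A non-significant detection result in the control-arm check would therefore be weak reassurance, though a reversal effect large enough to cancel the target gain would very probably be seen.

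The Step 2 identity rests on equal allocation and the rate-difference scale; on the log-odds scale of the planned model it is approximate. The power figures rest on the plan's own rates, sizes and design effect. The values of D are illustrations, and its sign is unknown.

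**What to change.** Leave the design and primary test unchanged.

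1. Describe the control arm as same order, half of it current practice.
2. Report D for cancer detection and recall with 95% confidence intervals, and base any statement about harm on the interval rather than on non-significance.
3. Pre-specify intervention versus both-forward control, for detection and recall, with 95% confidence intervals. Show it beside the primary result, and use it at least as a sensitivity input to the economic model.
4. Add a supportive reader-level analysis across all four groups: each reader's own recall decision and own flagged screen-detected cancers, by that reader's randomised direction, allowing for batch clustering. This compares about 550,000 with 550,000 women per reader position.

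The cost is two extra secondary analyses and a change of wording. Each reader's decision is already needed for the disagreement outcome, so no new data collection appears necessary. There are two drawbacks. The contrast with current practice is less precise than the primary (SE about 0.21 against 0.18 per 1,000). The reader-level outcome is not the double-read detection rate, so it can support the estimate of D but not replace it.

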### Power and sample size

Currently, 14,700 cancers are detected by screening each year, and the cancer detection rate is 7.8 per 1,000 women screened [3]. Detection of one extra cancer case per 2,000 women screened would increase the cancer detection rate to around 8.3 cancers per 1,000 women screened. To detect this change of 0.5 cancers per 1,000 women using a two-tailed test at 80% power and 5% significance, 501,361 women are required in each arm.

As randomisation occurs at the batch level, however, collected data are clustered and this must also be taken into consideration. The sample size of a clustered study must be increased by the design effect (DE), which is calculated as *DE* = 1 + (*m* - 1)*ρ* for a given intraclass correlation coefficient (ICC; *ρ*) and cluster size (*m*). The ICC was calculated using previous data in a logistic binomial Gaussian model (method B) with 1,000 Monte Carlo simulations [13]. Hence, using the ICC of 0.002 and a cluster (batch) size of 40 women produces a DE of 1.09, increasing the sample size required to 546,890 in each arm.

There is no adjustment for crossover, because once the intervention is applied to a screening centre, each batch will automatically be randomly assigned to the intervention or control group by the NBSS computer system and the intervention will be applied automatically by the same system. A woman could be lost to follow-up if her NBSS records have not been updated or if she is recalled from screening for further tests and does not attend her follow-up appointment. This is uncommon, however, so we have assumed low dropout rates of 3,500 women in each arm, inflating the sample required to 550,390 in each arm. Therefore, as detailed in Figure 1, the overall sample size required is for 1,100,780 women, or 44 breast screening centres for 1 year (On the basis that in England there are 82 centres each screening around 25,000 women per year).

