## Background

### Epidemiology and burden of breast cancer

Breast cancer is a leading cause of mortality in women and was the cause of death for 10,280 women in England and Wales in 2010. It was responsible for 12% of all deaths of women in their 50s and 8% of deaths of women in their 60s [1].

In England, up to 2.3 million women aged 47 to 73 years are projected to have breast cancer screening each year [2,3]. The recall rate is 40 per 1,000 women screened, and the cancer detection rate is 7.8 per 1,000 women screened; therefore, 32 healthy women per 1,000 screened are recalled for further tests (false-positive recalls) [3].

Currently, 66% of all breast cancers in women 50 to 64 years of age in England are detected by screening [3]. This occurs because some women choose not to be screened and the screening test is not perfect. Cancers diagnosed between screens (interval cancers) either grow *de novo* between screening rounds or are not seen or picked up by the programme. As with all screening programmes, the National Health Service Breast Screening Programme (NHSBSP) aims to keep interval cancers to a minimum, with a target rate of 2.3 per 1,000 women [4,5]. However, these are difficult targets; the rates achieved are closer to 3 per 1,000 women [6].

When investigating methods of improving cancer detection, one has to be mindful of the potential for increasing overdiagnosis and overtreatment (that is, cancers detected at screening and treated which never would have presented or caused problems within the patient’s life). It is important to ensure that any additional test or new methodology that increases cancer detection has a matched fall in interval cancer rates.

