### Statistical considerations

#### Primary analysis

To determine whether the cancer detection rate is higher in the intervention group than in the control group, a two-tailed analysis will be conducted using a multilevel logistic regression model. Levels in the model will be case, batch and centre. To prevent overfitting, each level will be included in the final model only if it explains a sufficient portion of the variability and improves model fit. The intervention may be more effective in certain subgroups, particularly younger women, women whose cases are read at the very beginning or end of the batch and the first batches to be examined in a workday. These subgroups will be analysed separately as specified in the statistical analysis plan and agreed by the Trial Steering Committee.

Analysis will be conducted as intention to treat, with all cases randomised included in the analysis. Missing data through loss to follow-up will occur in both groups for women who are recalled from screening but either did not attend the follow-up appointment or for whom no records exist in the database concerning the results of that appointment. Multiple imputation and sensitivity analyses to examine the effects of any missing data on the model will be considered if appropriate.

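### The allowance of 3,500 losses per arm is made on headcount, but the protocol places losses among recalled women, where all screen-detected cancers lie; with 3,500 losses, power is between about 73% and 80%

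*Protocol article*

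**What the plan says.** The Power and sample size section of the protocol article builds the target in three steps. From a control rate ("the cancer detection rate is 7.8 per 1,000 women screened") and an intervention effect that "would increase the cancer detection rate to around 8.3 cancers per 1,000 women screened", it states that "using a two-tailed test at 80% power and 5% significance, 501,361 women are required in each arm". A design effect then takes this to 546,890 per arm. Finally, loss to follow-up is described as rare and is covered by a fixed number: "we have assumed low dropout rates of 3,500 women in each arm, inflating the sample required to 550,390 in each arm".

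Two other sections bear on who these lost women are. Primary analysis says: "Missing data through loss to follow-up will occur in both groups for women who are recalled from screening". It then gives two routes, not attending the follow-up appointment or having no database record of its result. The Background section on epidemiology says: "The recall rate is 40 per 1,000 women screened, and the cancer detection rate is 7.8 per 1,000 women screened", and derives from this 32 healthy women recalled per 1,000.

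The sample size section and the legend of Figure 1 name similar routes, but there the route through records that were not updated is not expressly limited to recalled women.

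**The concern.** A headcount allowance works when losses are spread over everyone screened: the sample shrinks by 0.64% and 0.64% more women replace it. Here the outcome is rare and every screen-detected case has passed through recall. A recalled woman carries a risk of 7.8/40 = 19.5%, against 0.78% for a screened woman. Losing one recalled woman therefore removes, on average, 25 times as many expected cancers as losing one woman at random (19.5/0.78).

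For a rate below 1%, power depends almost entirely on the number of cancers counted. If the 3,500 are recalled women, the allowance replaces women but not the cancers lost with them. The stated 80% power is at stake, in a trial whose Discussion already concedes a risk of being underpowered and says the primary outcome may have to be replaced if recruitment targets are missed.

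**Working it through.** **Inputs.** Rates of 7.8 and 8.3 per 1,000, two-sided 5%, 80% power, 501,361, 546,890, 3,500 and 550,390 per arm (Power and sample size); recall of 40 per 1,000 (Background). Equal arms.

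**1. Reproduce the plan.** The two-proportion formula with pooled variance and no continuity correction gives 501,398 per arm, against 501,361 stated. The design effect implied by the plan's own totals is 546,890/501,361 = 1.0908. With it, 546,890 per arm gives 80.0% power. Then 546,890 + 3,500 = 550,390, as stated. The plan's chain holds, so what follows does not come from using a different formula. (ICC 0.002 and 40 women give 1 + 39 × 0.002 = 1.078 rather than 1.09; this moves power by only about half a point.)

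**2. Put the 3,500 on each base.**
- All women: 3,500/550,390 = 0.64%.
- Recalled women: 550,390 × 0.040 = 22,016, and 3,500/22,016 = 15.9%.

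**3. Cancers affected, if all 3,500 are recalled women and cancers are lost in proportion (f = 0.159).**
- Control: 550,390 × 0.0078 = 4,293 cancers, of which 3,500 × 7.8/40 = 682.5 are lost.
- Intervention: 550,390 × 0.0083 = 4,568 cancers, of which 0.159 × 4,568 = about 726 are lost.
- Observed rates: 7.8 × (1 − 0.159) = 6.56 and 8.3 × (1 − 0.159) = 6.98 per 1,000. The difference is 0.42 instead of 0.50.

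**4. Power.**
- Effective n per arm = 550,390/1.0908 = about 504,570.
- Standard error = √[(0.00656 × 0.99344 + 0.00698 × 0.99302)/504,570] = 0.0001633.
- z = 0.0004205/0.0001633 = 2.576; power = Φ(2.576 − 1.960) = 73.1%.
- With a design effect of 1.078 it is 73.6%. Keeping the lost women in the denominator as non-cancers, or removing them, gives the same 73.1%.
- 80% power under this loss would need about 651,000 per arm: 2 × 651,000/25,000 = about 52 centres, against 44 planned.

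**5. Relax the two assumptions (design effect 1.0908).** A smaller recalled share of the 3,500 and a lower relative loss of cancers both act through the fraction of cancers lost.

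| Cancers lost, relative to step 3 | Fraction of cancers lost | Power |
|---|---|---|
| 100% | 15.9% | 73.1% |
| 75% | 11.9% | 75.1% |
| 50% | 7.9% | 76.9% |
| 25% | 4.0% | 78.6% |
| 0% | 0% | 80.2% |

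**6. If loss is in fact rare.** The protocol gives no percentage, so these are assumed values, with cancers lost in proportion, at 550,390 per arm.

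| Recalled women lost | Women per arm | Power |
|---|---|---|
| 1% | 220 | 79.8% |
| 2% | 440 | 79.4% |
| 5% | 1,101 | 78.2% |

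**The case against.** A reader might infer that power is simply 73% and the stated 80% is an arithmetic error. The document does not support that, for three reasons.

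- **Who is lost.** The sample size section and the Figure 1 legend list records not updated as a route to loss without restricting it to recalled women. Primary analysis ties missing records to the recall appointment, so the article is ambiguous. Any of the 3,500 who were not recalled take no screen-detected cancers with them. This objection stands.
- **Whether cancers are lost in proportion.** The protocol does not say that recalled women with cancer go missing as often as recalled women without it. If they go missing less often, the power loss is smaller. This also stands.
- **The sums.** Every step reproduces within rounding. The fault is the base on which an allowance is expressed, not the addition. If loss is as rare as the text says, the number 3,500 is at fault and the power is nearly right.

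A reader might also infer that lost women are to be dropped from the analysis. Primary analysis says the opposite: all randomised cases are included, and multiple imputation and sensitivity analyses will be considered. The choice of imputation variables can properly be left to the statistical analysis plan. Imputation does not answer the power question, though, because it cannot recreate diagnoses that were never recorded. The Recruitment section's two months for follow-up appointments may well keep real losses low, which again argues for a number below 3,500.

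The Discussion's general admission that the trial may be underpowered concerns the effect size. It does not cover the loss allowance.

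**Conclusion.** The point holds in conditional form. A loss of 3,500 women per arm, a description of loss as rare, and 80% power do not fit together on the protocol's own rates if losses arise as Primary analysis describes. Power is about 73% when all 3,500 are recalled women and cancers are lost in proportion. It rises towards 80% as either assumption is relaxed, with about 77% if half as many cancers are lost. These figures take recall as 40 per 1,000 in both arms and a design effect of 1.0908; recall of 35 or 50 per 1,000 would move the lowest figure to 71.9% or 74.7%. The design, randomisation and analysis model are unaffected. What needs correcting is the stated loss assumption and the power that goes with it.

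**What to change.** In Power and sample size, state the expected loss as a share f of recalled women, say whether records not updated can concern women who were not recalled, and multiply both detection rates by (1 − f) instead of adding heads. Then choose one of two courses:

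- keep 3,500 and restate power as about 73%, with the range of 73% to 80% and the assumptions behind it; or
- replace 3,500 with a smaller, justified figure and restate sample size and power. At the assumed losses of 1%, 2% or 5% of recalled women, power at the planned size is 79.8%, 79.4% or 78.2%.

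Figure 1 should be brought into line. The cost is one paragraph and the figure, and a slightly less favourable stated power. No extra women are needed if power is restated at the planned size. Holding 80% exactly would need roughly 546,890/(1 − f) per arm, for example 546,890/0.98 = about 558,050 at 2%.
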